## SAFETY REPORTING OF ADVERSE EVENTS

### Adverse Event and Reporting Definitions:

[figure not shown]

Memorial Sloan-Kettering Cancer Center  
IRB Protocol

IRB#: 02-010A(8)

**(For Memorial Sloan-Kettering Cancer Center and Vanderbilt-Ingram Cancer Center)**

In the event of an adverse event, the first concern will be for the safety of the subject. Investigators are required to report to Genentech Drug Safety any serious adverse event, whether expected or unexpected, and which is assessed by the investigator to be reasonably or possibly related to or caused by Tarceva.

All events meeting these criteria will be reported for the time period beginning with any amount of exposure to Tarceva through the protocol-defined follow-up period. Serious criteria, definitions, and guidance for reporting follow.

An adverse event (AE) is any untoward medical occurrence in a subject participating in an investigational study or protocol regardless of causality assessment. An adverse event can be an unfavorable and unintended sign (including an abnormal laboratory finding), symptom, syndrome or disease associated with or occurring during the use of an investigational product whether or not considered related to the investigational product.

Serious adverse events (SAE) are adverse events occurring at any dose which meet one or more of the following serious criteria:

Results in death (i.e. the AE caused or lead to death)

Is life-threatening (i.e. the AE placed the subject at immediate risk of death; it does not apply to an AE which hypothetically might have caused the death if it were more severe)

Requires or prolongs inpatient hospitalization (i.e. the AE required at least a 24-hour inpatient hospitalization or prolonged a hospitalization beyond the expected length of stay; hospitalizations for elective medical/surgical procedures, scheduled treatments, or routine check-ups are not SAEs by this criterion)

Is disabling (i.e. the AE resulted in a substantial disruption of the subject's ability to carry out normal life functions)

Is a congenital anomaly/birth defect (i.e., an adverse outcome in a child or fetus of a subject exposed to the study drug prior to conception or during pregnancy)

It does not meet any of the above serious criteria but may jeopardize the subject and may require medical or surgical intervention to prevent one of the outcomes listed above

Expected adverse events are those adverse events that are listed or characterized in the current Investigator Brochure.

[figure not shown]

Memorial Sloan-Kettering Cancer Center  
IRB Protocol

IRB#: 02-010A(8)

Unexpected adverse events are those not listed in the current Investigator Brochure (I.B.) or not identified. This includes adverse events for which the specificity or severity is not consistent with the description in the I.B. For example, under this definition, hepatic necrosis would be unexpected if the I.B. only referred to elevated hepatic enzymes or hepatitis.

**MedWatch 3500 Reporting Guidelines:**

In addition to completing appropriate patient demographic and suspect medication information, the report should include the following information within the Event Description (section 5) of the MedWatch 3500 form:

**Amended: 7/13/04**

**Page 20 of 32**

[figure not shown]

Memorial Sloan-Kettering Cancer Center  
IRB Protocol

IRB#: 02-010A(8)

**Protocol description (and number, if assigned)**

**Description of event, severity, treatment, and outcome, if known**

**Supportive laboratory results and diagnostics**

**Investigator's assessment of the relationship of the adverse event to each investigational product and suspect medication**

Follow-up information:

- Additional information may be added to a previously submitted report by any of the following methods:
- Adding to the original MedWatch 3500 report and submitting it as follow-up.
- Adding supplemental summary information and submitting it as follow-up with the original MedWatch 3500 form.
- Summarizing new information and faxing it with a cover letter including subject identifiers (i.e. D.O.B. initial, subject number), protocol description and number, if assigned, brief adverse event description, and notation that additional or follow-up information is being submitted (The subject identifiers are important so that the new information is added to the correct initial report)

Occasionally Genentech may contact the reporter for additional information, clarification, or current status of the subject for whom and adverse event was reported. For questions regarding SAE reporting, you may contact the Genentech Drug Safety representative noted above.

Study Drug Relationship:

The investigator will determine which events are associated with the use of study drug. For reporting purposes, an AE should be regarded as possibly related to the use of the investigational product if the investigator believes:

- There is a clinically plausible time sequence between onset of the AE and Tarceva administration; and/or
- There is a biologically plausible mechanism for Tarceva causing or contributing to the AE.
- The AE cannot be attributed solely to concurrent/underlying illness, other drugs, or procedures.

**Reporting Requirements for IND Holders (Vanderbilt-Ingram Cancer Center only)**

a. Expedited IND Safety Reports:

[figure not shown]

Memorial Sloan-Kettering Cancer Center  
IRB Protocol

IRB#: 02-010A(8)

For Investigator Sponsored IND Studies, some additional reporting requirements for the FDA apply in accordance with the guidance set forth in 21 CFR § 312.32.

Events meeting the following criteria need to be submitted to the Food and Drug Administration (FDA) as expedited IND Safety Reports according to the following guidance and timelines:

***7 Calendar-Day Telephone or Fax Report:***

The Sponsor-Investigator is required to notify the FDA of any fatal or life-threatening adverse event that is unexpected and assessed by the investigator to be possibly related to the use of Tarceva. An unexpected adverse event is one that is not already described in the Investigator Brochure. Such reports are to be telephoned or faxed to the FDA and Genentech within 7 calendar days of first learning of the event. Each telephone call or fax transmission (see fax number below) should be directed to the FDA new drug review division in the Center for Drug Evaluation and Research or in the product review division for the Center for Biologics Evaluation and Research, whichever is responsible for the review of the IND.

***15 Calendar-Day Written Report:***

The Sponsor-Investigator is also required to notify the FDA and all participating investigators, in a written IND Safety Report, of any serious, unexpected AE that is considered reasonably or possibly related to the use of Tarceva. An unexpected adverse event is one that is not already described in the Investigator Brochure.

Written IND Safety Reports should include an Analysis of Similar Events in accordance with regulation 21 CFR § 312.32. All safety reports previously filed with the IND concerning similar events should be analyzed. The new report should contain comments on the significance of the new event in light of the previous, similar reports.

Written IND safety reports with Analysis of Similar Events are to be submitted to the FDA, Genentech Drug Safety, and all participating investigators within 15 calendar days of first learning of the event. The FDA prefers these reports on a MedWatch 3500 Form but alternative formats are acceptable (e.g. summary letter).

FDA fax number for IND Safety Reports:

[name]

All written IND Safety Reports submitted to the FDA by the Sponsor-Investigator must also be faxed to: Genentech Drug Safety

[contact] or [contact] (Please use the safety reporting fax cover sheet attached to this document for your fax transmission)

**b. IND Annual Reports**

In accordance with the regulation 21 CFR § 312.32, the Sponsor-Investigator shall within 60 days of the anniversary date that the IND went into effect submit a brief report of the progress of the investigation. Please refer to Code of Federal Regulations, 21 CFR § 312.32 for a list of the elements required for the annual report. All IND annual reports submitted to the FDA by the Sponsor-Investigator should be copied to Genentech. Copies of such reports should be mailed to:

Genentech, Inc.  
ATTN: [name]  
Tarceva IST Coordinator  
[name]  
[name]  
[contact]

[figure not shown]

Memorial Sloan-Kettering Cancer Center  
IRB Protocol

IRB#: 02-010A(8)

Retention of Records

U.S. FDA regulations (21 CFR 312.62[c]) require that records and documents pertaining to the conduct of this study and the distribution of investigational drug, including CRFs, consent forms, laboratory test results, and medication inventory records, must be retained by the Principal Investigator for 2 years after marketing application approval. If no application is filed, these records must be kept 2 years after the investigation is discontinued and the U.S. FDA and the applicable local health authorities are notified.

**12.0 CRITERIA FOR THERAPEUTIC RESPONSE/OUT COME ASSESSMENT**

For the purposes of this study, patients will undergo repeat CT scanning of all indicator lesions following four and eight weeks of OSI-774 therapy. Thereafter, CT scanning will be obtained every eight weeks. See Appendix F for methods of response assessment and classification.

**13.0 CRITERIA FOR REMOVAL FROM STUDY**

If at any time the patient develops progressive disease he/she will be taken off study and referred for alternative therapy.

If at any time the patient develops unacceptable toxicity he/she will be removed from study.

If at any time the patient is found to be ineligible for the protocol as designated in the section on Criteria for Patient/Subject Eligibility (i.e., a change in diagnosis), the patient will be removed from the study.

Administration of radiotherapy or of any other chemotherapeutic drug during the trial will result in the patient being taken off study.

The patient will be taken off study if he/she withdraws consent. If at any time the patient develops any condition that would, in the judgment of the investigator, affect assessments of clinical status to a significant degree or would pose undue risk to the patient through continuation, the patient will be removed from the study.

[figure not shown]

## 14.0 BIOSTATISTICS

This will be a multicenter non-randomized single arm phase II trial seeking to determine whether OSI-774 results in a meaningful proportion of responses accompanied by symptomatic relief and improved quality of life in patients for whom no other standard therapy is available or commonly effective.

Patients will be asked to complete the Lung Cancer Symptom Scale at baseline and during the trial. Changes in the mean 100 mm visual analogue scale scores measuring disease-related symptoms for patients will be recorded weekly for the first four weeks of treatment and monthly thereafter. Nine symptoms (hemoptysis, pain, appetite, cough, dyspnea, activity, quality of life, fatigue, and lung cancer symptoms) will be recorded. Each patient's score on a given symptom will undergo square-root transformation to stabilize variance, followed by calculation of the difference from baseline to weeks 2, 3, 4, 5 and "best" timepoint. We have previously reported disease-related symptom improvement with this method [Miller, Cancer, 75(4), 1995].

A response rate of 15% or greater would be of interest in this patient population. An objective response rate of  $\geq 25\%$ , in conjunction with significant improvements in the LCSS may warrant consideration for regulatory submission. A complete response rate  $\geq 10\%$  would also warrant further study. A 2-stage design will be utilized. At the first stage, a total of 21 patients will be enrolled. If  $\geq 1$  response is noted, an additional 29 patients will be recruited to the second stage. This design assures that if no response is observed in the first 21 patients the likelihood of the true response rate being  $> 15\%$  is  $< 5\%$ . If  $\geq 12$  patients in the total sample of 50 patients demonstrate an objective response or  $\geq 5$  patients demonstrate a complete response, the sample size will be increased to 100 patients so as to provide better precision around the objective response rate and to generate additional safety and QOL data via the LCSS.

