## 2.0 OBJECTIVES AND SCIENTIFIC AIMS

- To determine the major objective response rate (p.r + c.r.) of OSI-774 in bronchioloalveolar carcinoma of the lung using a Fleming two-step trial design.
- To measure the quality of life in this population using the LCSS.
- To measure the duration of response and the time to disease progression in this population.
- To measure the median survival in this patient population.

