## 10.0 EVALUATION DURING TREATMENT/INTERVENTION

Please see study flow chart (**Appendix A**)

During the first 4 weeks of OSI-774 therapy, patients will be seen on a weekly basis (+/- 3 working days if the patient is unable to be seen for logistical reasons such as holidays, etc). Thereafter, doctor visits and labs, including CBC, electrolyte and chemistry profile with liver function tests, will be every 4 weeks until completion of treatment. CT scanning of all indicator lesions will be performed every 8 weeks in order to determine response to OSI-774 or progression of disease. Patients will undergo repeat ECG at the end of treatment. The Lung Cancer Symptom Scale (LCSS) will be administered at baseline and every week for the first five weeks. After the ninth week, the LCSS will be administered every 4 weeks until the end of study. The LCSS patient form requires a second grade reading level and takes an average of 8 minutes to initially administer, including instruction time. Once a patient has become familiar with filling it out, it takes only 3-5 minutes to complete. The LCSS is designed as a disease- and site-specific measure of quality of life with lung malignancies and their effect on overall symptomatic distress, functional activities, and global quality of life. The LCSS consists of two scales: one completed by the patient and an optional one for health care professionals ("counterpart observer") to provide context. Only the patient scale will be administered in this study. The nine-item patient scale includes nine visual analogue scales (100-mm horizontal line) where the patient puts a mark on a line to indicate intensity of response to the items in question (0 = lowest rating; 100 = highest rating). One LCSS sub-score is the average symptom burden index computed as the mean score for all six major symptoms (loss of appetite, fatigue, cough, dyspnea, hemoptysis, and pain). Time to symptomatic progression will be measured in terms of a worsening in this index.

[figure not shown]

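### Section 14 does not say which of 45 LCSS changes counts as a significant improvement, and the 'best' timepoint favours improvement even when nothing has changed

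*Protocol*

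**What the plan says.** Section 14.0 (Biostatistics) lists the items: "Nine symptoms (hemoptysis, pain, appetite, cough, dyspnea, activity, quality of life, fatigue, and lung cancer symptoms) will be recorded". They are handled one at a time: "Each patient's score on a given symptom will undergo square-root transformation to stabilize variance". Five changes per item are then taken on that scale, by "calculation of the difference from baseline to weeks 2, 3, 4, 5 and 'best' timepoint". The same section says that a response rate of 25% or more, "in conjunction with significant improvements in the LCSS may warrant consideration for regulatory submission".

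Neither Section 14.0 nor any other section says which item, which timepoint or how many items must improve, or at what significance level. Section 2.0 gives only a general aim: "To measure the quality of life in this population using the LCSS".

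Section 10.0 does define a summary score: "One LCSS sub-score is the average symptom burden index computed as the mean score for all six major symptoms". Its only stated use is for deterioration: "Time to symptomatic progression will be measured in terms of a worsening in this index". Section 14.0 does not mention it.

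**The concern.** Nine items at five timepoints give 45 separate changes, and "significant improvements in the LCSS" could refer to any of them. When one favourable result out of many is enough, a drug with no effect on symptoms can appear to improve them.

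The 'best' timepoint raises a different problem. A timepoint picked because it looks best shows an average gain even when nothing has changed, so a test of that gain against zero is biased as well as repeated.

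Section 14.0 describes the trial's purpose as finding responses that come with symptom relief and better quality of life. The trial has one arm, so no control group would reveal a chance gain. At stake is whether the LCSS result adds anything to the response rate.

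**Working it through.** **The plan's own error figure.** Section 14.0 gives one error probability, and it concerns response. With no responses in 21 patients, a true response rate above 15% is said to have a likelihood below 5%. At a true rate of 15%, P(0 of 21) = 0.85^21 = 0.033, so the figure holds. There is no corresponding figure for the LCSS.

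**Inputs from the protocol.** Nine items; weeks 2, 3, 4, 5 and 'best'; 21 patients at the first stage, 50 in total, 100 if expanded. Contrasts: 9 × 5 = 45, of which 9 × 4 = 36 are at fixed weeks and 9 are at 'best'.

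**Assumptions, because the protocol gives no figures.**
- Two-sided 5% per contrast, so 2.5% in the favourable direction, with no multiplicity adjustment.
- Paired t-tests on normally distributed scores with no missing data.
- Correlation between items 0 to 0.7, and between visits 0.5 to 0.8.
- 'Best' means each patient's own best change over the four visits.

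**Ceiling for fixed weeks.** If all contrasts were independent, P(at least one false improvement) = 1 − 0.975^k. This is 20.4% for k = 9, 59.8% for k = 36 and 68.0% for k = 45. The contrasts share a baseline and are correlated, so these figures are too high.

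**Fixed weeks with correlation.** Simulated trials with no true change, 50 patients, 1,500 trials per cell, at least one false improvement among the 36 contrasts:

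| Item correlation | Visit correlation 0.5 | Visit correlation 0.8 |
|---|---|---|
| 0 | 51.0% | 51.9% |
| 0.3 | 40.7% | 41.8% |
| 0.5 | 34.3% | 34.4% |
| 0.7 | 27.5% | 27.2% |

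Repeat runs differ by a point or two, so the range is about 25% to 52%. If two different items must improve, it is about 13% to 17%.

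**The 'best' contrast.** Write a score as a patient level plus visit noise with standard deviation s. With no true change:
- The best of four visits lies on average 1.029s above the patient's level, with variance 0.492s².
- Subtracting the baseline adds variance s², so the best change has mean 1.029s and SD √1.492 s = 1.221s.
- The standardised false gain is 1.029 / 1.221 = 0.843. Both s and the visit correlation cancel.
- The t statistic has noncentrality 0.843√n: 3.86 for n = 21 and 5.96 for n = 50, against critical values of 2.09 and 2.01.
- The chance of false significance per item is therefore about 96% at n = 21 and above 99.9% at n = 50.

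The simulation agrees: 95.5% to 96.3% per item at n = 21 and essentially 100% at n = 50. At least one of the nine 'best' contrasts is significant in 99.8% to 100% of null trials.

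**One named comparison.** A single composite at one week gave a false improvement in 1.8% to 3.5% of simulated trials, in line with the nominal 2.5%. Bonferroni over the fixed weeks would need 0.05/36 = 0.0014 per contrast. It would not repair 'best', whose expected value is above zero with no true change.

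**The case against.** Several objections have force.

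- **No test is specified.** Section 14.0 says that differences are calculated. Testing is implied only by the word significant. The LCSS is a secondary measure, and details of its tests are commonly left to an analysis plan. That would answer mere silence. Here, though, the protocol itself fixes the 45 contrasts and the criterion, with nothing to connect them.
- **The criterion is tentative and has two parts.** A reader might infer that a regulatory case could be made on a chance LCSS result. The text does not support that. A response rate of at least 25% is also required, and meeting both only opens the question of submission. The rules for continuing (1 response in 21) and expanding (12 responses or 5 complete responses in 50) use response alone.
- **'Likely by chance' is too strong for the fixed weeks.** At n = 50 the rate exceeds one half only when items are uncorrelated, which is implausible because quality of life, activity and overall lung cancer symptoms overlap the specific symptoms. The wording is also plural, and requiring two items lowers the rate to about 13% to 17%. Near-certainty comes only from 'best'.
- **'Best' is not defined.** If it meant one week chosen for the whole group from weeks 2 to 5, it would add no false positives beyond the fixed-week figures. The per-patient reading fits better, because the sentence begins with each patient's score.
- **A reader might infer that the index is the more powerful measure.** That depends on how widely benefit is spread. If k of six symptoms improve equally with equal SDs, the index's signal-to-noise relative to one affected item is (k/6)/√((1+5r)/6). For r = 0.5 to 0.3 this is 0.44 to 0.52 at k = 2 and 0.65 to 0.77 at k = 3. It clearly exceeds 1 only from k = 5. No general power advantage can be claimed.

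**Conclusion.** The point holds in limited form. The LCSS part of the Section 14.0 criterion is not interpretable as written. The fixed weeks alone raise the false-improvement rate from 2.5% to about 25% to 52% at n = 50, or about 13% to 17% under a two-item reading. If a per-patient 'best' counts, an LCSS improvement is almost guaranteed without any true change.

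The sizes rest on the assumed 2.5% tail, the assumed correlations, and normal, complete data. The bias of a per-patient 'best' does not depend on the correlations. The primary endpoint, the accrual rules and the response-rate part of the criterion are unaffected. What is lost is the evidence that the LCSS was meant to add to the response rate.

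**What to change.** In Section 14.0, state that the only LCSS comparison counting toward the criterion is change from baseline in the average symptom burden index defined in Section 10.0, at one fixed week such as week 5. Give the significance level, and say whether the index is analysed on the raw or the square-root scale. Identify the assessment meant, because Section 10.0 describes weekly forms for the first five weeks and Section 14.0 for the first four. Report item-by-week changes descriptively with confidence intervals. Define 'best' and exclude it from inference.

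The cost is a few sentences, with no new data, visits or patients. The price is that single-item claims become descriptive, and the index is less sensitive than a single item if benefit is confined to a few symptoms.

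### The LCSS change to an undefined 'best' timepoint is biased towards improvement and is not kept out of the LCSS criterion for regulatory submission

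*Protocol*

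**What the plan says.** Protocol Section 14.0 (Biostatistics) describes a "multicenter non-randomized single arm phase II trial". For the LCSS, a set of 100 mm visual analogue scales, it states: "Nine symptoms (hemoptysis, pain, appetite, cough, dyspnea, activity, quality of life, fatigue, and lung cancer symptoms) will be recorded". The handling is per patient and per item: "Each patient's score on a given symptom will undergo square-root transformation to stabilize variance". On that transformed scale the section then calls for "calculation of the difference from baseline to weeks 2, 3, 4, 5 and 'best' timepoint". The *best* timepoint stands in the same list as the four fixed weeks. It is not defined, and no allowance is made for having selected it.

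The next paragraph of Section 14.0 says that a response rate of at least 25%, "in conjunction with significant improvements in the LCSS may warrant consideration for regulatory submission". It does not say which of the listed differences has to be significant.

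Section 10.0 sets the assessment schedule: "The Lung Cancer Symptom Scale (LCSS) will be administered at baseline and every week for the first five weeks", and "After the ninth week, the LCSS will be administered every 4 weeks until the end of study". Section 2.0 lists quality of life measured by the LCSS as an objective, separate from the response rate.

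**The concern.** A change to a patient's best later score compares one baseline reading with the most favourable of several readings. If scores fluctuate from visit to visit, the most favourable of several lies on the good side of a single reading by construction. Zero is then not the value to expect when the drug does nothing for symptoms, and any ordinary test of zero change takes over that shift. In a randomised trial the control arm would show the same shift and it would largely cancel. Here there is no control arm.

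This matters because "significant improvements in the LCSS" is one of two conditions attached to a possible submission, and the text leaves the biased difference eligible to meet it. A response rate that truly meets its condition could be accompanied by a symptom benefit that is partly or wholly an artefact of selection.

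**Working it through.** **The plan's own figure.** The only error figure in Section 14.0 concerns response: no response in 21 patients if the true rate is 15%. This is 0.85^21 = 0.033, below the stated 5%, so it reproduces. No error figure is given for the LCSS.

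**Inputs from the protocol.** Single arm; differences per patient and per item on the square-root scale; four fixed weeks (2, 3, 4, 5); n = 21 at stage 1, 50 in total, 100 if expanded.

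**Assumed inputs, not in the protocol.** *Best* is the patient's own most favourable score among K post-baseline visits. A paired t-test is used at two-sided 0.05, so 2.5% in the favourable direction. Baseline mean is 35 mm, between-patient SD 20 mm, within-patient SD s = 5 to 16 mm. Scores are clipped to 0–100 mm. Lower is taken as better; the argument is symmetric for items scored the other way.

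**Step 1: direction of the bias, free of any SD.** With no true change, the baseline and the K later scores are exchangeable. For continuous scores the best later score beats baseline with probability K/(K + 1): 4/5 = 80% of patients for K = 4 and 9/10 = 90% for K = 9. Without bias this would be 50%.

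**Step 2: size before clipping.** The expected minimum of four independent standard normal values is −1.03, with variance 0.49. The false mean gain is therefore 1.03 × s, that is 5.2 mm at s = 5 and 16.5 mm at s = 16.

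**Step 3: why the test rejects whatever the SD.** The SD of (baseline − best of four) is s × √(1 + 0.49) = 1.22 s. The expected t statistic is about (1.03/1.22) × √n, and s cancels:
- n = 21: 0.844 × 4.58 = 3.9, against a critical value of 2.09.
- n = 50: 0.844 × 7.07 = 6.0, against 2.01.

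**Step 4: simulation under no true change** (clipped scale, square-root transformation, paired t-test):

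| Comparison | n | False mean gain | Significant in favour of drug |
|---|---|---|---|
| Best of 4 visits | 21 | about 5–15 mm | 90–92% |
| Best of 4 visits | 50 | about 5–15 mm | about 99.9% |
| Best of 8 visits | 50 | about 7–20 mm | 100% |
| One fixed visit | 50 | 0 | 2–3% |

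Assumptions expressed as a correlation between visits (0.3 to 0.97, normal scores, no transformation) give the same picture: 95–96% at n = 21 with K = 4, and 99.9–100% at n = 50 or 100. For an item near the floor of the scale (mean 5 mm, SD 10 mm, K = 5, n = 50) the false gain shrinks to 2–5 mm, but the test still rejects in 99.9–100% of trials.

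**Step 5: the other reading of *best*.** If it means the one week with the best group mean, the favourable false-positive rate at n = 50 is about 7–15% per item for K = 4 to 9. That is inflated above 2.5% but far from certain.

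**Step 6: the response condition.** At n = 50, 25% means at least 13 responses (12/50 = 24%, 13/50 = 26%). The chance of 13 or more is 7.5 × 10⁻⁷ at a true rate of 5%, 0.001 at 10% and 0.03 at 15%.

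**The case against.** The strongest reply is that the protocol prescribes the calculation of differences and nothing more. It names no test, p-value or alpha for the *best* difference, and does not say that this difference decides the LCSS condition. The four fixed-week differences in the same sentence do not have the bias, and details of testing may sit in a SAP that is not shown. All of this stands. The protocol leaves the biased difference eligible; it does not choose it. But some test of these differences is implied once significant improvement is asked for, and none of the five is excluded.

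*Best* is also undefined. The wording about each patient's score favours the per-patient reading without settling it, and the group-week reading has the much smaller inflation shown in step 5.

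A reader might infer more than the documents support:
- *An inert drug would reach submission on this measure.* It would not. The LCSS condition is joined to the response condition, which an inert drug would almost never meet (step 6). The wording is also only permissive, and the stage-1 and expansion rules use response alone.
- *The test would declare improvement even when patients get worse.* That depends on an SD the protocol does not give. With a true 5 mm worsening, n = 50 and four visits, improvement is declared in about 2% of trials at within-patient SD 5 mm, about 50% at 8 mm and about 86% at 12 mm.
- *Patients who stay on study longer gain more.* This is true only if *best* extends beyond week 5. The Section 10.0 schedule would allow that, but Section 14.0 does not say so.
- *An apparent improvement is guaranteed.* The expected group change is biased, but single patients can show no gain, and at n = 21 about one trial in ten would not reach significance.

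**Conclusion.** The point holds in a limited form. Section 14.0 lists a difference that, on its more natural reading, favours the drug when nothing has changed. It does so in a design with no control arm, and the difference is not kept out of the LCSS condition. The direction of the bias needs no assumption beyond some visit-to-visit variation within patients. Its size in millimetres and the rejection rates rest on the assumed mean, SDs and paired test, and on the per-patient reading of *best*.

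The consequence is a possible overstatement of symptom benefit for a drug that does produce responses. This should be fixed, but it is not critical: the primary endpoint and the rules for continuing or expanding the trial are unaffected.

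**What to change.** Add one sentence to Section 14.0. It should say that the LCSS criterion rests on change from baseline at one prespecified visit already planned (for example week 5), or on the average of weeks 2 to 5. It should add that the *best* difference is descriptive only, with no p-value and no role in that criterion. Naming a single contrast also stops a choice among the four fixed weeks, which without adjustment would give about 6–10% favourable false positives per item.

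No new data or visits are needed. The cost is a less favourable-looking LCSS result. The change should be made before LCSS results are seen, because a contrast chosen afterwards would carry little weight.
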